**Figure 2 F2:**
[figure not shown]
Transcutaneous tibial nerve stimulation (TTNS) intervention. Pictures of the TTNS device, cables and electrode placements. (A) The TTNS device has two channels that can be adjusted independently. Electrodes are placed in a specified, standardised order (1–4). (B) Lateral view of the foot, showing the electrode placement on the dorsal bone and plantar fat pad of the fifth metatarsophalangeal joint. (C) Medial view of the foot, electrodes are placed 4–5 cm proximal and posterior to the medial malleolus, as well as in the longitudinal arch of the foot, distal to, and in line with, the medial malleolus.

The TTNS intervention is performed for 30 min/day, 5 days/week, starting within 40 days after SCI and ending after all 3-month follow-up assessments have been completed (total intervention period: 6–9 weeks). The majority of the participants are expected to be inpatients for the duration of the intervention, a setting that maximises participant adherence. The application of the TTNS intervention by designated and trained personnel ensures that the treatment is applied correctly while blinding is maintained. In addition, the remaining follow-up visits are part of standardised SCI care in all four participating centres, limiting the potential loss to follow-up, and ensuring that the participants receive necessary ancillary care.

Participants may be withdrawn when the study protocol is not followed, a health problem occurs with a suspected link to the stimulation, if a severe health condition/illness makes an intensive outpatient treatment or new hospitalisation necessary, consent is withdrawn, or if a pregnancy is detected. Any concomitant treatment and medication intake will be carefully documented, so that the information can be used in secondary analyses.

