DO, detrusor overactivity.

Generally, the outcome assessments are administered at screening and baseline as well as during each of the three follow-up visits (figure 1). One notable exception is the bladder biopsy, which will take place at baseline and the 6-month follow-up visit, and only with additional consent. Moreover, during the intervention period, participants will complete some of the questionnaires once per week, and the bladder and bowel diaries once every 2 weeks. Withdrawal from the study can occur at any time if treatment for NDO is indicated. If withdrawal occurs, all study completion assessments should be performed whenever possible. Furthermore, the trial is nested in the SwiSCI cohort study, so observation of the participants will continue through the cohort study after the end of TASCI. SwiSCI can provide long-term, open-label outcome data regarding morbidity, activities and participation (eg, labour market participation), QoL and life expectancy.

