### Sample size

Presuming a proportion of spontaneous success among the sham group of 0.15,^23^ 114 participants (57 verum, 57 sham) need to be included to detect a difference of 0.25 in the proportion of participants who develop NDO, and thereby to correctly reject the null hypothesis with a probability (power) of 0.8. The type I error probability associated with the test of this null hypothesis is 0.05. Since the primary outcome variable is binary, this sample size analysis included a continuity correction to avoid type I error inflation.

Using prospective data collected by the SwiSCI inception cohort for the years 2014–2016 and applying a modified version of the TASCI inclusion/exclusion criteria, a total of 193 eligible patients are predicted during the 3-year recruitment period of TASCI. Anticipating a recruitment rate of 66%, this implies that the requisite 114 participants can be included within 3 years. Expected participant numbers per centre during the study period are 20 for Basel, 42 for Nottwil, 13 for Sion and 39 for Zürich. Moreover, these data imply that participants who withdraw or drop out can be replaced.

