### Statistical analyses

The primary analysis will be an intention-to-treat analysis. The general statistical methodology for primary and secondary outcomes comprises basic descriptive statistics and multivariable regression analyses. Continuous variables will be tested for normality, and displayed as either means and SD or medians and ranges; categorical variables will be displayed as frequencies and proportions. Multivariable regression techniques will be employed to control for possible confounding due to unequal distribution of baseline parameters across the trial arms, as well as systematic variation in outcomes across RCT strata, that is, centre and LEMS. Longitudinal analysis techniques (eg, mixed-effect models, structural equation models for growth and time-to-event models) will be used to account for repeated measures, facilitating time-updated covariate adjustment and appropriately modelling trends with respect to time.

The primary outcome ‘the occurrence of NDO jeopardising the UUT 1 year after SCI’ is a binary response variable, which will be described using proportions with 95% binomial CIs and analysed using logistic regression, thus expressing treatment effect sizes as ORs (with 95% CIs). Sensitivity analyses will include a time-to-event analysis to evaluate the impact of TTNS on the risk of early drop-out or preterm endpoints (<1 year). Protocol non-adherence, early withdrawals and loss to follow-up will be examined and used to inform per-protocol sensitivity analyses. Subgroup analyses stratified on LEMS or study centre may be performed if an intervention–subgroup interaction is found, with the understanding that these analyses will likely be underpowered. In cases where outcome data are used in an observational context, usually to examine prognosis or NLUTD aetiology, causal claims will be supported by an underlying theoretical framework.

Multiple imputation will be used when appropriate to account for missing data in the predictor variables.^38^ Pattern mixture models may be applied to address missing outcome data for different scenarios of the missing data process.^39^ Sensitivity analysis will be used to evaluate the robustness of the chosen imputation strategy. Any sensitivity analyses added after the breaking of the blind (post-hoc sensitivity analyses) will be clearly identified as such in the trial report.

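### Study withdrawal is allowed when NDO treatment is indicated, so 6- and 12-month secondary data can go missing because of the primary outcome itself

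*Protocol article*

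**What the plan says.** **Withdrawal.** In the protocol article, the Outcomes section (text after Table 2) states: "Withdrawal from the study can occur at any time if treatment for NDO is indicated". Completion assessments are then to be done where feasible, with no time point given. The same paragraph notes that participants stay under observation in the SwiSCI cohort. The Intervention section has its own list of withdrawal reasons, and NDO treatment is not on it.

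**Primary outcome.** The Outcomes section defines a composite: NDO of at least 40 cm H2O at urodynamics, or the start of NDO treatment, at one year or earlier.

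**Schedule.** Stimulation lasts 6–9 weeks and ends once the 3-month assessments are complete. Nearly every outcome in Table 2 is also due at 6 and 12 months. Of the later visits, the Intervention section says that "the remaining follow-up visits are part of standardised SCI care in all four participating centres".

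**Analysis.** The Statistical analyses section plans an intention-to-treat primary analysis, longitudinal models and, as an option, pattern mixture models for missing outcomes. It adds: "Protocol non-adherence, early withdrawals and loss to follow-up will be examined and used to inform per-protocol sensitivity analyses".

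**The concern.** The trigger for leaving the study overlaps with the event that the trial is designed to prevent. Once stimulation has ended at about 3 months, there is no study treatment left to stop. From then on, withdrawal from the study can only mean that later visits are lost.

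Participants who remain at 6 and 12 months would then be selected by a post-randomisation event that TTNS is meant to influence. Comparisons of bladder and bowel symptoms, sexual function, quality of life, imaging and biomarkers among them would no longer be fully protected by randomisation. Longitudinal models would have to rely on assumptions about values after NDO treatment that were not observed in those who left. The secondary and mechanistic aims depend on this follow-up.

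**Working it through.** **Inputs from the Sample size section**
- Sham success: "Presuming a proportion of spontaneous success among the sham group of 0.15", so the sham event proportion is 1 − 0.15 = 0.85.
- Effect: "to detect a difference of 0.25 in the proportion of participants who develop NDO", so verum success is 0.15 + 0.25 = 0.40 and the verum event proportion is 0.60.
- Size: "114 participants (57 verum, 57 sham) need to be included".
- Power 0.8 and type I error 0.05, with a continuity correction. Sidedness is not stated.

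**Step 1. Reproduce the plan's figure.** Two-sided, with mean proportion 0.275:

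n′ = [1.960·√(2·0.275·0.725) + 0.842·√(0.15·0.85 + 0.40·0.60)]² / 0.25² = 48.9

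With the continuity correction, n = (n′/4)·[1 + √(1 + 4/(n′·0.25))]² = 56.6, which rounds up to 57 per arm or 114 in total. This matches, so the proportions are read as the plan intended.

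**Step 2. Expected primary events.** Sham 57 × 0.85 = 48.5; verum 57 × 0.60 = 34.2; total 82.7 of 114 (72.5%).

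**Step 3. Loss of 12-month secondary data.** Let f be the share of primary events that lead to withdrawal with no usable 12-month assessment. The article gives no value for f, so the range is an assumption. Loss per arm = f × event proportion. The detectable standardised difference is (1.960 + 0.842)·√(1/n₁ + 1/n₂), for 80% power and two-sided 0.05.

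| f | Loss, sham | Loss, verum | Loss, overall | Remaining, sham / verum | Detectable difference |
|---|---|---|---|---|---|
| 0 | 0% | 0% | 0% | 57 / 57 | 0.52 SD |
| 0.25 | 21% | 15% | 18% | 44.9 / 48.4 | 0.58 SD |
| 0.5 | 42.5% | 30% | 36% | 32.8 / 39.9 | 0.66 SD |
| 0.75 | 64% | 45% | 54% | 20.7 / 31.4 | 0.79 SD |
| 1 | 85% | 60% | 72.5% | 8.6 / 22.8 | 1.12 SD |

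Overall loss passes one half only when f > 0.5/0.725 = 0.69.

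**Step 4. Difference between arms.** The excess loss in sham is f × 0.25, that is 12.5 points at f = 0.5 and 25 points at f = 1. It arises only if the assumed effect is real. With equal event rates and the same f, loss would be equal by arm but still related to the outcome.

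**Step 5. Month 6.** The article gives no timing of events, so loss at 6 months cannot be calculated.

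**Step 6. Passages set side by side.** The Outcomes section makes NDO treatment a ground for withdrawal; the list in the Intervention section does not. The withdrawal sentence refers to treatment being indicated, whereas the composite counts its initiation.

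**The case against.** The other side has a good deal to say.

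- **Withdrawal is permissive.** It is tied to treatment, not to every primary event. An amplitude finding alone need not lead to exit, and an event first found at the 12-month visit costs no 12-month data. This stands, and it rules out two readings that a reader might infer: that most participants will lack 12-month data, and that the plan expects 85% v 60% to withdraw. Those figures are assumed event proportions and serve only as ceilings on the loss.
- **The primary outcome is protected.** The event is already counted at exit, and the analysis is by intention to treat. The time-to-event secondary outcome is likewise determined at the event. This stands.
- **There are safeguards.** Completion assessments may supply some data, SwiSCI observation continues, and pattern mixture models are available. They help only in part. The assessments are not mandatory and their timing is not fixed, and a value taken at exit is not a 12-month value. SwiSCI is described as open-label, and the domains listed do not include urodynamics, electrophysiology or biomarkers. The pattern mixture models are optional and rest on assumptions.
- **Per-protocol analysis.** A reader might infer that primary events will be removed from the per-protocol set because they count as early withdrawals. The article says only that such withdrawals inform those analyses. It states no exclusion, and the definition can properly sit in the SAP. No criticism is made on that point.

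**Conclusion.** The point holds as a should-fix matter limited to the 6- and 12-month secondary outcomes other than time to event. As written, the withdrawal provision lets follow-up end on a trigger that overlaps with the primary event, and it leaves the timing of completion assessments open. Missing secondary data can then depend on the outcome and, if TTNS works, be more frequent in sham.

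The size is not known. The ceilings are those in the last row of the table. The likely loss depends on f, which the article does not give. The arm difference also rests on the planned effect being true and on f being the same in both arms. The detectable differences describe loss of precision only; any selection bias comes on top and cannot be quantified from the document.

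**What to change.** Amend the withdrawal sentence in the Outcomes section to say that:
- the start of NDO treatment is recorded as a primary event, with its date and type;
- it does not by itself end study follow-up;
- the scheduled 6- and 12-month assessments are still done in participants who continue to consent;
- for those who do leave, completion assessments are done at a stated time point.

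State that secondary outcomes are analysed in all randomised participants regardless of NDO treatment. Reconcile the sentence with the withdrawal reasons in the Intervention section, and settle whether indication or initiation of treatment is meant. This concerns data collection only; no clinical rule is proposed.

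**Cost.** A short amendment. The sample size stays at 114 and patient care is unchanged. The visits are described as standard care, but the article does not say that of the research-only assessments (such as EEG, TMS, MRI and biomarkers), so these continue in the affected participants as already scheduled. Some secondary measurements will be taken on NDO treatment and must be interpreted as such. The article describes recruitment as ongoing; 12-month values not collected from participants who leave cannot be recovered later.

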### Sample size

Presuming a proportion of spontaneous success among the sham group of 0.15,^23^ 114 participants (57 verum, 57 sham) need to be included to detect a difference of 0.25 in the proportion of participants who develop NDO, and thereby to correctly reject the null hypothesis with a probability (power) of 0.8. The type I error probability associated with the test of this null hypothesis is 0.05. Since the primary outcome variable is binary, this sample size analysis included a continuity correction to avoid type I error inflation.

Using prospective data collected by the SwiSCI inception cohort for the years 2014–2016 and applying a modified version of the TASCI inclusion/exclusion criteria, a total of 193 eligible patients are predicted during the 3-year recruitment period of TASCI. Anticipating a recruitment rate of 66%, this implies that the requisite 114 participants can be included within 3 years. Expected participant numbers per centre during the study period are 20 for Basel, 42 for Nottwil, 13 for Sion and 39 for Zürich. Moreover, these data imply that participants who withdraw or drop out can be replaced.

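### Replacement of leavers is the only sample-size provision for loss: 114 has no attrition margin, and the wording covers non-adherent participants and participants who have already had the primary event

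*Protocol article*

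**What the plan says.** Four parts of the protocol article bear on this.

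- **Sample size.** The section asks for 114 participants, 57 per arm, and gives no loss rate. After the recruitment forecast it adds: "Moreover, these data imply that participants who withdraw or drop out can be replaced".
- **Statistical analyses.** "The primary analysis will be an intention-to-treat analysis". Withdrawals, non-adherence and loss to follow-up are to inform per-protocol sensitivity analyses. Pattern mixture models are an option for missing outcomes.
- **Intervention (text after Figure 2).** "Participants may be withdrawn when the study protocol is not followed". Other listed grounds include a health problem thought to be linked to the stimulation, severe illness, pregnancy and withdrawn consent.
- **Outcomes.** "Withdrawal from the study can occur at any time if treatment for NDO is indicated". On withdrawal, the end-of-study assessments are to be done where feasible. The same section makes the start of NDO treatment a component of the primary outcome, at whatever time it occurs in the year.

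The article does not say whether a replaced participant stays in the intention-to-treat set, or whether 114 counts participants randomised or participants with an observed outcome.

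**The concern.** A one-year trial normally allows for loss in the number randomised. Here the only allowance in the sample-size section is replacement, and it applies without exception to anyone who withdraws or drops out. Two groups matter.

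- **Non-adherent participants.** They can be taken out of the study, not just off the intervention. An assessment at exit, done if feasible, does not replace urodynamics at 12 months. Adherence may be related to arm and to prognosis, so these gaps are selective. A new participant fills the place but says nothing about the outcome of the one who left.
- **Participants withdrawn because NDO treatment is indicated.** Under the Outcomes definition they are primary events, not losses. There is nothing to replace, and replacing and omitting them would delete events.

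At stake are the validity of the primary comparison, if replaced participants were omitted, and the stated power, if they are not replaced.

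**Working it through.** **Inputs (Sample size section).** "Presuming a proportion of spontaneous success among the sham group of 0.15"; the 114 "need to be included to detect a difference of 0.25 in the proportion of participants who develop NDO", which gives success of 0.15 v 0.40; the trial is "to correctly reject the null hypothesis with a probability (power) of 0.8"; alpha is 0.05. A continuity correction is stated. Sidedness is not. Allocation is 1:1 (Randomisation and blinding).

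**Step 1: reproduce 114.** With p̄ = 0.275 and d = 0.25, the uncorrected size per arm is

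n′ = [1.960·√(2·0.275·0.725) + 0.842·√(0.15·0.85 + 0.40·0.60)]² / 0.25² = 48.9.

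The continuity correction gives

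n = (n′/4)·[1 + √(1 + 4/(n′·d))]² = (48.9/4)·[1 + √(1 + 4/(48.9·0.25))]² = 56.6, so 57 per arm and 114 in total.

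This matches the plan exactly for a two-sided test (a one-sided corrected test would need 47 per arm). No attrition margin is included.

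**Step 2: effect of loss.** The documents give no loss rate, so the rates below are assumptions. The power columns assume that 114 are randomised, that nobody is replaced and that only observed outcomes are analysed. Corrected power is Φ{[0.25 − 1/n − 1.960·√(2p̄(1−p̄)/n)] / √(0.3675/n)}, where n is the number per arm with an outcome and 0.3675 = 0.15·0.85 + 0.40·0.60. The uncorrected figure omits the 1/n term. The last column is 114/(1 − loss), rounded up, with the equal-arm total in brackets.

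| Assumed loss | n per arm | Power, corrected | Power, uncorrected | Randomised total to keep 114 observed |
|---|---|---|---|---|
| 0% | 57.0 | 0.80 | 0.86 | 114 |
| 5% | 54.1 | 0.78 | 0.84 | 120 |
| 10% | 51.3 | 0.75 | 0.82 | 127 (128) |
| 15% | 48.4 | 0.72 | 0.80 | 135 (136) |
| 20% | 45.6 | 0.69 | 0.77 | 143 (144) |

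**Step 3: room for replacement.** The forecast is 193 × 0.66 = 127.4, about 13 above 114. It covers losses up to 1 − 114/127.4 = 10.5%. The expected numbers per centre in the same paragraph sum to 20 + 42 + 13 + 39 = 114, which leaves no room.

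**Step 4: what happens if participants with events were replaced and left out.** The scenarios are illustrative; the documents do not describe them.

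- Ten events omitted from each arm of 67: verum (0.40 × 67)/57 = 26.8/57 = 0.470; sham (0.15 × 67)/57 = 10.05/57 = 0.176. The difference moves from 0.25 to 0.29.
- One in five events omitted from each arm: verum 0.40/(0.40 + 0.8·0.60) = 0.455; sham 0.15/(0.15 + 0.8·0.85) = 0.181. The difference moves to 0.27.
- Ten events omitted from verum only: verum moves from 0.40 to 0.47 and sham stays at 0.15, so the difference moves to 0.32.

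Even omission that treats both arms alike inflates the effect.

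**The case against.** The sentence on replacement closes the recruitment forecast and says only that replacement is possible. It removes nobody from the analysis. A reader might infer that leavers are bound to be replaced, that this contradicts intention-to-treat, or that the analysed set or the power will certainly be wrong. The documents do not support any of these. Enrolling extra participants while keeping everyone randomised is fully compatible with intention-to-treat, and it keeps power near 0.80 if losses stay within about 10.5%. Participants who start NDO treatment cost no power when counted as events. The planned rates imply about 0.85 × 57 + 0.60 × 57 = 83 events among 114, so a surplus of about 13 can hardly have been meant to replace them all.

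The plan also has other protections: end-of-study assessments on withdrawal, follow-up visits within routine care, optional pattern mixture models and sensitivity analyses. Without the continuity correction, power stays at about 0.80 up to 15% loss. Finally, this is an article without its full protocol or analysis plan, which may define the analysis set.

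All of this stands as a limit on how strongly the point can be put. It does not dispose of it. The number to be included and the replacement sentence are stated text, and that sentence makes no exception for participants with events. Taking non-adherent participants out of the study is also stated text. It creates missing 12-month outcomes that neither extra recruits nor an optional missing-data model can recover.

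**Conclusion.** The point holds as a weakness in what the plan fixes, not as a demonstrated error. The figure of 114 is arithmetically right for its inputs but contains no margin for loss. The replacement wording reaches participants who have had the primary event. Withdrawal for non-adherence makes 12-month outcomes selectively missing, and replacement does not repair that.

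The power loss is conditional. Corrected power is about 0.75 at an assumed 10% loss and 0.69 at 20%, if leavers are not replaced and only observed outcomes are analysed. The bias is also conditional: it arises only if replaced participants are omitted. In the illustrative scenarios that affect both arms, it adds 0.02 to 0.04 to a target difference of 0.25.

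**What to change.** 1. **Sample size.** State that every randomised participant is analysed in the assigned arm, whether or not further participants are enrolled. State that a participant with a primary event, including the start of NDO treatment, is counted as an event and never replaced.
2. **Intervention.** Separate stopping the intervention from leaving the study, so that non-adherent participants are followed to the 12-month urodynamics unless they withdraw consent. When the intervention itself is stopped is a clinical matter and is not addressed here.
3. **What 114 counts.** Choose one option:
   - Define 114 as the number with an observed primary outcome, and give an assumed loss rate and the randomised total: for example 127 at 10%, or 128 with equal arms. The forecast of 127 just about covers this. The per-centre figures, which sum to 114, would need to be reconciled with it.
   - Keep 114 randomised and restate power as about 0.75 at an assumed 10% loss (about 0.82 without the continuity correction).

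The change should be made before unblinding. It costs a few sentences, a little more follow-up of non-adherent participants and a slightly less favourable stated figure. The extra randomised participants are no more than replacement would have used.
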